### Secondary outcome

Secondary outcomes will be general mental health (depression and anxiety), psychological variables (cognitions related to OCD, self-efficacy), and psychosocial variables (quality of life, functional impairment). We expect that individuals randomised to receive iCBT, compared to matched controls, will demonstrate significantly greater improvements in secondary outcome measures from pre- to post-intervention. We also expect iCBT to be associated with lower service utilisation than the matched control condition.

Demographic and clinical variables, treatment credibility and expectations of treatment, treatment acceptability, working alliance between patient and therapist, and attitudes towards homework tasks will also be assessed. We expect that: a) participants will rate iCBT as more credible and acceptable than the matched control group, but that there will be no differences between groups on working alliance and attitudes towards homework; and b) outcomes will be positively associated with homework completion, but other predictors (e.g. education, gender, age, degree to which other treatments were undertaken) are not expected to contribute to outcomes. Finally, the present study proposes to explore how individual patient characteristics may influence therapeutic outcomes (e.g., demographic variables, functional impairment, treatment readiness, personality, diagnostic/symptom severity, specific symptom presentation, levels of comorbidity, expectancies of treatment credibility).

## Methods/design

The study will evaluate the acceptability and efficacy of iCBT compared to a matched control condition. The RCT will randomise 212 individuals who fulfil inclusion criteria into either the active treatment or control condition, for 12 weeks duration (Figure 1). Outcomes for participants in both groups will be assessed at baseline (Time = 0) and post-intervention (Time = 12 weeks). Participants in iCBT will be further assessed at follow-up (Time = 6-to-12 months), while participants in the control will be crossed over to receive the intervention and assessed at post-intervention (Time = 24 weeks) and follow-up (Time = 9 months).

**Figure 1 Fig1:**
[figure not shown]
**CONSORT flowchart.**

### Ethics approval

The present study proposal has been subject to peer review and approval by the National Health and Medical Research Council (Project Grant Application 620506). Ethics approval has been obtained from the Human Research Ethics Committees from Swinburne University of Technology (No. 2010/104).

### Participants

Recruitment will occur in all states and territories of Australia, and will be open to all Australian residents aged 18 years and over. Two hundred and twelve individuals with a primary diagnosis of OCD, as indicated by structured clinical interview, will be recruited through widespread media coverage, internet advertising (e.g., Facebook), web search engines (e.g., Google) and referrals from other online treatment services (e.g., Anxiety Online, Mental Health Online; [49]). Consumer organisations and mental health services/professionals (e.g., university psychology clinics, divisions of general practice, psychiatric facilities, private psychologists and psychiatrists) will be approached to promote the program and invited to make referrals.

### Eligibility criteria

All interested participants will be required to complete a telephone interview and fulfil Diagnostic and Statistical Manual for Mental Disorders (DSM-IV) criteria for OCD on the Structured Clinical Interview for DSM-IV (SCID) [50]. All participants will be required to have sufficient English to complete treatment and assessments without translation, provide multiple contact details, be able and willing to access internet and email, and consent to follow up assessments. Comorbid diagnosis of other disorders will be permitted where OCD is the primary diagnosis, and the non-OCD diagnosis is not in the extremely severe range. Exclusion criteria include meeting criteria for current psychosis, substance abuse, head injury or neurological disorder, and active suicidal ideation. Checks with participants about other treatments received will be maintained during the study.

### Sample size calculation

Given previous research showing large effects for online CBT for OCD [43, 45], we expect a large effect for iCBT (i.e., 33% achieving clinically significant change in YBOCS scores; Cohen’s d of approximately 1.0). Progressive relaxation training (PRT) will be the active attention control [51]. PRT has demonstrated inconsistent effectiveness in treating OCD with studies indicating low [52] and high efficacy [53]. Given this, we anticipate a moderate effect size for this group (i.e., 15% achieving clinically significant change in YBOCS scores; Cohen’s d approximately 0.5). Therefore, 88 individuals per intervention group will be sufficient to detect a difference in effects between iCBT and control at post-intervention, assuming significance is set at 5% (α = 0.05) power at 80% and a standard deviation of 5 for the distribution of mean change. We include an additional 20% (N = 18 per group) to allow for attrition and potential effects of various extraneous influences, such as protocol adherence; 106 participants per group will be required (total = 212).

### Participant recruitment procedure

Participants will make initial contact via email or telephone. Those who express an interest will be emailed a Participant Information and Consent Form. Consenting participants will be asked to provide contact details to arrange the telephone interview (to assess eligibility and collect baseline measures). At the telephone interview, those participants not meeting criteria will be given information about alternative treatment and relevant local services and internet sites. If participation criteria are met, consent will be sought for further baseline assessment, treatment and follow-up.

### Randomisation procedure

In accordance with CONSORT guidelines [54], randomisation will occur after participants have completed their baseline measures. Although there is a generally equal gender prevalence of OCD in adults, there are inconsistent reports of gender differences in service utilization rates [55]. Therefore, stratified randomisation will be used in order to minimize the differences in gender distributions across and within groups. This will be done via computer software and entered by an independent researcher. Participants will be allocated to a therapist and given immediate access to their online condition (intervention or control), and participants in the control condition given access to the intervention after completing the post-intervention assessment. The CONSORT diagram of the study design is shown in Figure 1.

### Study arms

Throughout the course of the study, participants from both the intervention and control groups will continue to receive treatment as usual (TAU). Structured checks with participants about other treatments will be maintained at all assessment points with assessors blind to condition. Both groups receive an online program consisting of 12 modules over 12-weeks. Participants will be encouraged to complete one module per week for the duration of treatment. Both groups will receive online information, weekly homework tasks, downloadable worksheets and audio files. All participants will receive weekly email support from a remote therapist who will monitor progress, review homework, provide support and encouragement, and give assistance in tailoring the treatment to the participant’s individual problem, in line with the online content of their allocated condition. The communication will be restricted to one therapist email per week, although users will be able to email their therapists as often as they wish. Treatment will be via automated programs. Assessors and therapists will be licenced psychologists, or supervised students enrolled in a Masters or Professional Doctorate in Clinical Psychology. Therapy provision and assessment will be conducted with independent assessors. All therapists will be trained and supervised on a fortnightly review basis by a Clinical Psychologist experienced in the treatment of OCD. Email therapy sessions will be saved and rated by independent assessors to assess treatment fidelity, and interrater reliability assessments will be conducted to confirm diagnosis.

### Intervention: Therapist-assisted internet-based cognitive behavioural therapy (iCBT)

The intervention is a 12-week internet-based cognitive behavioural therapy. Modules 1–3 provide information about OCD, anxiety, and an introduction to CBT, along with anxiety and depression management strategies (e.g., relaxation, activity scheduling). In Modules 4–6, Exposure and Response Prevention (ERP) strategies are introduced through the construction of fear hierarchies. These teach the participant to plan and implement an ERP program suited to their individual needs. Due to the heterogeneity of the disorder, participants are provided with a range of examples to correspond to various presentations. Modules 7–9 include cognitive therapy techniques (e.g., cognitive restructuring) targeting OCD specific cognitive styles (such as inflated responsibility/overestimation of threat, importance/control of thoughts). As part of this, cognitive misappraisals are identified and alternatives developed and practiced; and more advanced ERP, integrating cognitive strategies is undertaken. Modules 10–12 include relapse preventions strategies (e.g., problem solving, risk identification, contingency management, and mindfulness techniques). The importance of daily practice is emphasised and discussions focus on enablers of, and barriers to, maintenance of CBT.

### Control: Therapist-assisted internet-based progressive relaxation training (iPRT)

The matched control condition is an internet-based treatment for anxiety adapted from Bernstein et al. [56]. Participants initially receive basic information about OCD, the relationship of OCD to anxiety, and the use of relaxation to manage anxiety. Individuals are then taught to relax specific muscle groups while paying attention to the feelings associated with both the tensed and relaxed stages. The program teaches the individual to achieve a state of deep relaxation in increasingly shorter periods and to control excess tension in stress-inducing situations. Participants work through the sequential tensing and releasing of 16 muscle groups (Modules 1 to 3). These groups are reduced to seven (Modules 4 and 5) and to four (Modules 6 to 7). The tension component is then withdrawn (Modules 8 to 11) in what is called “relaxation through recall”, and the final stage (Module 12) consists of a mental summary of the previously learned techniques. Participants will have access to downloadable audiovisual and written material to guide their progressive relaxation training. Although relaxation training has previously not been considered effective for OCD [52], recent research supports that progressive relaxation can be effective [53]. Considering that the program requires more than attention and engagement, the term ‘matched control’ was deemed a more appropriate descriptor than ‘active attention placebo’.

### Measures

Outcomes will be assessed via clinician-rated telephone interview at baseline, post-intervention and follow-up. Throughout the intervention and control, participants will self-report secondary outcomes through an online questionnaire embedded within Modules 1, 5, 9 and 12 of each condition. Instruments used to collect data from participants, including primary and secondary outcomes, are listed in Table 1.

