### Cognitive behaviour therapy for OCD

In targeting such processes in cognitive-behaviour therapy (CBT), patients monitor thoughts, evaluate evidence for maladaptive beliefs and appraisals, and develop and practice more productive appraisals to counter cognitive biases. Behavioural experiments and other cognitive techniques that help test alternative interpretations of intrusions are a key strategy in the treatment of OCD [7], but these techniques are somewhat more specialised and less accessible than the more widely known exposure-based strategies [8]. Exposure and Response Prevention (ERP) is an evidence-based central behavioural technique requiring individuals to face situations that induce distress while refraining from engaging in compulsive rituals [9, 10]. In doing so, ERP leads to the extinction of avoidance and anxiety responses. Anxiety management and coping strategies such as relaxation techniques also have some credibility and acceptability amongst patients as they are useful in decreasing anxiety; however, they are generally no longer centrally utilised in CBT programs as the evidence for their efficacy is inconsistent, although they may be useful when the person has extreme anxiety responses [10].

Current clinical guidelines recommend CBT as a first line treatment for OCD [11]. CBT programs are typically 12 – 24 hours duration, with drop-out rates of around 25% and recovery rates at post-treatment of 50% to 75% [10]. Systematic reviews and meta-analyses support that CBT programs are effective in reducing OCD symptoms, with effect sizes ranging from 0.8 to 1.24 from pre to post treatment [10–15]. Although effective treatments exist, only a small percentage (<10%) of individuals with OCD receive CBT [16–18]. The mean duration between onset of first OCD symptoms and presentation for treatment is around seven years [19, 20]. Individuals may go undiagnosed and untreated for many years due to a failure of health professionals to recognise OCD [21] and to intense feelings of embarrassment and guilt motivating patients to not disclose their experiences [16, 22]. For those that do present for help, access to evidence-based treatment is poor; a shortage of appropriately qualified professionals (especially in geographically remote areas), long waitlists, and individuals’ financial constraints mean that specialised evidence-based treatment is often unavailable [8].

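### Five self-report measures, including acceptability, have a post-treatment score only for participants who reach Module 12, so their arm comparisons are exposed to bias

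*Protocol article*

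**What the plan says.** The Measures section gives two collection routes. The first is by telephone: "Outcomes will be assessed via clinician-rated telephone interview at baseline, post-intervention and follow-up". The second is online: "participants will self-report secondary outcomes through an online questionnaire embedded within Modules 1, 5, 9 and 12 of each condition". No self-report collection outside the modules is described, and the self-report half of Table 1 has module numbers, not weeks, as its column headings.

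Module pace is not fixed. Under Study arms, "Participants will be encouraged to complete one module per week for the duration of treatment".

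On the order of events, Randomisation procedure says that "randomisation will occur after participants have completed their baseline measures", and Trial status gives the same order. Randomisation procedure also says that, once allocated, participants are "given immediate access to their online condition (intervention or control").

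The Secondary outcome section reads: "Secondary outcomes will be general mental health (depression and anxiety), psychological variables (cognitions related to OCD, self-efficacy), and psychosocial variables (quality of life, functional impairment"). It adds hypotheses on service utilisation, acceptability and alliance. The current study section makes acceptability part of the primary aim.

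Data analysis plans intention-to-treat and completer analyses, then a longitudinal hierarchical linear model chosen so that missing data need not be imputed, and an examination of attrition bias.

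**The concern.** A score stored inside Module 12 exists only for someone who gets that far. Getting that far is a result of treatment: people may stop because the program is unhelpful, unacceptable or no longer needed. iCBT and iPRT differ greatly in content, so unequal completion is plausible. For a measure taken only at Modules 1 and 12, the arm comparison then rests on two self-selected groups, not on the randomised groups. Acceptability is the sharpest case, because those who found the program unacceptable are the most likely to be missing from the final rating.

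A second question is whether the first self-report scores were taken before or after allocation. A module of the allocated condition cannot be opened before the condition is assigned, yet baseline is said to be complete before randomisation.

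**Working it through.** **The plan's own figure.** The only calculation stated is the sample size. With 33% v 15%, two-sided 5%, 80% power and a pooled variance under the null:

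n = [1.960 × √(2 × 0.24 × 0.76) + 0.842 × √(0.33 × 0.67 + 0.15 × 0.85)]² / 0.18² ≈ 87.2, so 88 per group, as stated.

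Adding 20% gives 88 × 1.2 = 105.6, so 106. This concerns the telephone-rated YBOCS and is not affected by the present point.

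**What depends on the modules (Table 1).**

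| Measure | Telephone version | Modules |
|---|---|---|
| AQoLS, BDQ, SULRQ, TEI, WAQ | none | 1 and 12 |
| OBQ, DASS | none (depression and anxiety also have HRSD and HRSA) | 1, 5, 9, 12 |
| GSES | none | 1 only |
| YBOCS, OCI | yes | YBOCS 1 and 12; OCI 1, 5, 9, 12 |
| SCID, HRSD, HRSA | telephone only | – |

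Of the six named secondary domains, four have no telephone instrument: OCD cognitions, self-efficacy, quality of life and functional impairment. Adding service utilisation makes five of seven.

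**What the hierarchical model can use.** For OBQ and DASS, a participant who stops after Module 5 or 9 still contributes a later value. For the five measures in the first row, a participant who stops at Module 11 contributes the Module 1 value only. The model can then correct only for what that first value predicts.

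**Possible size.** Let c be the proportion reaching Module 12, and let completers score d SD better than non-completers. The arm mean is c × (completer mean) + (1 − c) × (non-completer mean), so the completer mean is too favourable by (1 − c) × d. Between arms the shift is (c₁ − c₀) × d in favour of the arm with lower completion. The document gives neither c nor d, so both are assumed:

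- c = 0.75: 0.25 × 0.3 = 0.075 to 0.25 × 1.0 = 0.25 SD.
- c = 0.55: 0.45 × 0.3 = 0.135 to 0.45 × 1.0 = 0.45 SD.
- Difference: 0.20 × 0.3 = 0.06 to 0.20 × 1.0 = 0.20 SD.
- Equal c and equal d: zero.

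At these rates, 106 × 0.75 = 79.5 and 106 × 0.55 = 58.3 participants per arm would have Module 12 data.

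**Check with another model.** If completion is a normal latent variable correlated r with outcome, the completer mean shifts by r × φ(z)/c, where z is the c-quantile. With r = 0.2 to 0.5 (assumed), 65% v 80% gives 0.044 to 0.110 SD and 60% v 80% gives 0.059 to 0.147 SD. The order of magnitude is the same.

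**Order of baseline and allocation.** Randomisation procedure and Trial status put baseline first. Measures and Table 1 put the first self-report set in Module 1 of each condition, and Randomisation procedure opens the condition after allocation. Both cannot hold for OBQ, DASS, GSES, AQoLS, BDQ and SULRQ if Module 1 is their only first collection. For CEQ, TEI, WAQ and the homework scale, which rate the allocated program, a first value after allocation is natural.

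**The case against.** The strongest reply is that the important outcomes are protected. Both primary outcomes, and depression and anxiety, are rated by telephone whatever module has been reached. This stands, and it limits the severity.

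The plan also has a method for incomplete data. A reader might infer that intention-to-treat analysis is impossible for every self-report outcome. The document does not support that: OBQ and DASS have Module 5 and 9 values, and the hierarchical model can use them under missing at random. The reply does not rescue the measures taken only at Modules 1 and 12.

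The sizes rest on assumptions. The drop-out of around 25% in the background section describes CBT programs in the literature; this trial's own allowance is 20%, and neither is a module-completion rate. Nor should the shift be set against the 0.5 gap between the effects assumed for the two arms (1.0 and 0.5), which concerns the YBOCS. The formula also describes a completers-only mean, not the hierarchical model. All this stands, so the figures are illustrations.

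On baseline, a reader might infer that first scores were certainly given with allocation known. The recruitment section mentions further baseline assessment after the telephone interview, which could be an online set completed before randomisation. What is shown is a conflict in the text.

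A reader might also infer that slow control participants cross over before finishing iPRT. Module pace allows it, but no section describes it.

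**Conclusion.** The point holds for AQoLS, BDQ, SULRQ, TEI and WAQ: as the collection rule is written, a post score depends on finishing the program. Their between-arm comparisons, including the acceptability part of the primary aim, are exposed to bias. It is not established that they are biased. Under the stated assumptions a completers-only comparison could be shifted by 0.06 to 0.20 SD towards the arm with lower completion. The direction reverses if completers do worse than non-completers, and the shift vanishes if completion is equal and equally selective.

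OBQ and DASS are affected less. The telephone-rated YBOCS, SCID, HRSD and HRSA are not affected, so a reading that the trial's main result is compromised has no support. The order of baseline and randomisation needs reconciling for six measures. GSES is a separate gap: Table 1 marks it at Module 1 only, so no pre-to-post change can be computed for anyone. Severity: should be fixed.

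**What to change.** - **Participants still in the treatment period:** send the Module 5 and 9 sets at weeks 5 and 9, and the Module 12 set at week 12, by emailed link to everyone randomised, whatever module they have reached. The control arm's week-12 set should be completed before iCBT access is opened. This keeps the order already stated, in which access follows the post-intervention assessment.
- **Participants not yet randomised:** collect OBQ, DASS, GSES, AQoLS, BDQ and SULRQ before randomisation. Leave CEQ, TEI, WAQ and the homework scale after allocation.
- **Participants already past week 12:** adjust for the pre-randomisation telephone scores (YBOCS, OCI, HRSD, HRSA) and report the Module 1/12-only measures as program-completer data.
- **Text:** reconcile Randomisation procedure and Trial status with Measures and Table 1 on when the first self-report set is taken.

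The cost is a change to the questionnaire trigger, reminder emails and a short amendment; no new instruments are needed. With 179 of 212 randomised at the time of writing, the pre-randomisation change reaches at most 212 − 179 = 33 people; the calendar links also reach those still in treatment. The downside is two collection regimes in one trial, which must be reported.

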**Table 1 Tab1:** **Instruments used for data collection**

Measurement tools/questions		Time point			
Clinician administered (telephone)		Baseline	Post-treat		Follow-up
Demographics	Age, gender, postcode, family characteristics, religion, education, general medical history	x			
Current treatment	Current physiological & psychological treatment	x	x		x
Diagnosis	Structured Clinical Interview for DSM-IV Axis I Disorders - Clinician Version (SCID-IV) [50]	x	x		x
OCD severity	Yale-Brown Obsessive-Compulsive Scale (YBOCS) [44]	x	x		x
	Obsessive-Compulsive Inventory (OCI) [57]	x	x		x
	Clinical Global Improvement Scale (CGI) [58]	x	x		x
Mental health	Hamilton Rating Scale for Depression (HRSD) [59]	x	x		X
	Hamilton Rating Scale for Anxiety (HRSA) [60]	x	x		x
